### Participant Recruitment and Retention

Peer workers will visit sites and provide information to both staff and potential participants about the study to encourage recruitment. Service staff will be asked to refer potential participants (at any stage of their treatment) to the study via the peer worker. Additional recruitment strategies will be by advertising (e.g., flyers, newsletters, online via service websites) and peer workers attending community meetings and other events to inform potential participants directly about the study to encourage self-referral.

For those who meet eligibility criteria and decide to participate in the study, the peer worker will gain written informed consent from the participant. Provision is made on the consent form for opting in or out of possible participation in a qualitative study of experiences of trying to stop smoking and for participation in further studies.

Telephone follow-up and compensation for completed assessments will aid in increasing retention rates. Monthly check-in texts (to remind participants to inform the researchers if their contact details change) will be conducted to help maintain contact with participants, and 3 monthly follow-up will assist with accurate participant recall of smoking and quitting history. Participants will receive a $40 gift card for baseline and for each completed follow-up assessment and a $40 gift card for the 8-month face-to-face assessment for biochemical verification of self-reported smoking cessation (if required).

Upon completion of the baseline assessment, the peer worker will provide standard smoking care (described above) to all participants. The peer worker will then access the randomization allocation for the participant via the eCRF program, and communicate appropriately with the participant.

### Randomization

Following completion of the baseline assessment, a brief intervention will be delivered by a peer worker—prior to randomization—to ensure all participants receive the recommended minimum standard care, in a manner that is unbiased by the outcome of randomization. Following this, the computer program used to complete the baseline will randomize to condition using 1:1 randomization. Participants will be randomly allocated to either no further intervention, or to be contacted by Quitline who will offer a targeted callback counseling intervention with NRT provided, over an 8-week period. As stated above, cluster randomization will be used in situations where risk of contamination is higher, such as residential services, stratified by short- or long-term residence, with 1:1 allocation. Individual randomization will be used in services where contamination of risk is lower, via permutated block sizes of 4 and 6 to avoid incomplete blocks, stratified for site. Participants will be allocated a unique computer-generated study number. Randomization will be independently managed by the trial epidemiologist (JA) and uploaded to a web-based data capture tool (Research Electronic Data Capture; REDCap) that will also have case report forms (eCRF) created for the project using REDCap.

Following randomization, those in the intervention group will be told of the additional supports they will be getting (see above). Controls will be simply told the session is over and reminded of when the first follow-up survey might be expected.

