**Key**

* *If not captured at previous assessment*.

***E** Extracted data*.

***S** Current smokers*.

***$** If used Quitline*.

***A** Those reporting abstinence*.

***I** Selected subsample*.

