### Sample Size Determination

Based on our previous study (23) which achieved a 15% prolonged abstinence rate in depressed smokers, and knowing rates are considerably less among those with more severe mental illnesses (62) we anticipate that for the primary outcome of prolonged abstinence at 8 months, prolonged abstinence will occur in 1% of the control arm vs. 8% in the intervention arm. To detect this effect with 80% power at *p* = 0.05, we require 134 per arm. We expect ~30% attrition, inflating the sample size to 191/arm or 382 overall. Thus, we will recruit 382 smokers over 36 months and follow up at 2-, 5-, and 8-months post-baseline, completing the study over a 4.5-year period.

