### Blinding

Outcome assessors will be blinded to study design and allocation and will have training and regular supervision on practices to maintain blinding in a PROBE design study. These have been previously used successfully by our team (63). Importantly, outcomes assessors will ask participants about smoking outcomes prior to any questions about use of cessation supports, questions that often produce answers which can indicate likely experimental condition.

The mental health practitioners, follow-up assessors, qualitative interviewers, and Quitline counselors are located in separate organizations, which will maximize maintenance of the outcomes assessors' blindness to study design and treatment allocation. Outcomes assessors will access only contact details, and not treatment files. The eCRF permissions will not allow outcomes assessors to access information about the participant's treatment allocation.

Participants will be aware of what support they are receiving, but not of the comparison condition due to the “limited disclosure” approach. Participants will be informed about what is involved (i.e., the follow-up assessments) and that they may be offered support with smoking cessation. They will not be informed of the specifics of the support (i.e., intervention will receive proactive referral to Quitline and be supplied with NRT). Control participants will be informed of the options available and encouraged to follow up on any they are interested in, in the usual manner (GP/other health professional/self-referral to Quitline). The outcomes assessment team will remain blinded to treatment allocation until completion of the study. Data analysts will be blinded by labeling the intervention conditions “A” and “B.”

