### Limitations

There are three main limitations associated with this trial. Firstly, due to cluster randomization of residential sites, the peer workers will become aware of each site's allocation. Peer workers will be carefully trained and supervised not to communicate this information. They will also be supervised so as to encourage equal recruitment across control and intervention sites. Secondly, outcome to 8-months has been chosen as the focus of this study so as to examine medium term smoking, which parallels that for well populations (67). However, it would be informative to follow the sample over a longer timeframe to measure longer-term health and other benefits.

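### At cluster-randomised residences, later residents are enrolled and given the brief intervention by a peer worker who knows their arm, and question order protects assessor blinding only within a single call

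*Protocol article*

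**What the plan says.** **Recruitment and allocation.** Under Participant Recruitment and Retention, the peer worker obtains consent, gives standard smoking care after the baseline assessment, and then opens the allocation. Intervention Training and Supervision lists baseline assessment among the tasks for which peer workers are trained. The Randomization section says the brief intervention comes before randomization "to ensure all participants receive the recommended minimum standard care, in a manner that is unbiased by the outcome of randomization". The Unblinding section puts the unblinding of peer workers after baseline and the brief intervention. Neither section makes an exception for residential services, which are randomised as clusters.

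The Limitations section says that, "due to cluster randomization of residential sites, the peer workers will become aware of" each site's allocation. The safeguards it gives are training and supervision not to pass the information on, and supervision towards equal recruitment in the two arms.

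**Outcome assessment.** The Blinding section says: "The outcomes assessment team will remain blinded to treatment allocation until completion of the study". Its specific safeguard against revealing answers is that "outcomes assessors will ask participants about smoking outcomes prior to any questions about use of cessation supports", and it accepts that such questions can point to the likely condition. Table 1 schedules the item on products and services (including NRT and Quitline) at baseline, 2, 5 and 8 months. It schedules WAIT-3, the alliance scale for the Quitline counselor, at 2 months, with the key entry "If used Quitline". The primary outcome is taken at 8 months: an interview about last smoking, then CO testing of those who report abstinence.

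**The concern.** Two protections are stated more firmly than the procedures support.

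The first is protection at entry. In a cluster-randomised site the arm of a resident not yet enrolled is already fixed. Once the peer worker knows it, the decision whom to approach, how to present the study, how to run the baseline interview and how thoroughly to give brief advice can all be affected. The arms may then differ in motivation or dependence before treatment starts. The brief intervention, which is the whole of the control condition, may also be given differently by arm.

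The second is protection at the endpoint. Six-month sustained abstinence rests on an interview answer, as do most of the secondary outcomes. An assessor who heard about Quitline calls and supplied NRT at 2 or 5 months may have a view of the likely arm by the 8-month call. Asking outcomes first in that later call does not undo this.

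**Working it through.** **Step 1. The plan's own figure.** Sample Size Determination assumes that "prolonged abstinence will occur in 1% of the control arm vs. 8% in the intervention arm" and states "80% power at *p* = 0.05, we require 134 per arm". With the unpooled variance formula, two-sided 0.05:

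n = (1.960 + 0.842)² × (0.01×0.99 + 0.08×0.92) / 0.07² = 133.8, so 134 per arm.

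For attrition, 134 / 0.70 = 191.4; the article has "We expect ~30% attrition, inflating the sample size to 191/arm or 382 overall". The figure reproduces, and this point does not alter it.

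**Step 2. How many participants the recruitment issue can reach.** Inputs from Statistical Methods:

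| Group | Count |
|---|---|
| Individually randomised | 150 |
| Short-term programs | 10 × 15 = 150 |
| Long-term programs | 6 × 10 = 60 |
| Total described | 360 |

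The total is 360 here against 382 in Sample Size Determination; 360 is used because only it is broken down by setting.

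- Upper bound, if every site's arm is known before anyone there is enrolled: 150 + 60 = 210, and 210/360 = 58%.
- If the arm becomes known after the first enrolment in each of the 10 + 6 = 16 programs: 210 − 16 = 194, which is 194/360 = 54% of the total and 194/210 = 92% of residents.

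The article does not say when a site's arm is released, so the second line is an assumption.

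**Step 3. The recruitment passages side by side.** For an individually randomised participant the order (consent, baseline, brief intervention, allocation) keeps the peer worker unaware until the end. For a later resident of a cluster site, Limitations says the peer worker already knows the allocation, while Randomization and Unblinding imply that this is not so. Both cannot hold for that resident. Supervision towards equal recruitment addresses numbers. It does not address who is chosen or how the brief intervention is delivered.

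**Step 4. The blinding passages call by call.**

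| Call | Possible clues heard at earlier calls | Does question order protect this call's outcomes? |
|---|---|---|
| 2 months | none | yes |
| 5 months | NRT/Quitline use and WAIT-3 at 2 months | not if the same assessor calls |
| 8 months (primary) | the above, plus NRT/Quitline use at 5 months | not if the same assessor calls |

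The Blinding section keeps assessors from treatment files and allocation fields. It does not deal with what they heard at an earlier call.

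**Step 5. What CO testing covers.** Under Primary Outcome, a reading of 8 ppm or higher indicates recent smoking, and only those who report abstinence are tested. CO can overturn a false report of current abstinence. It cannot confirm the preceding months, and it is never applied to someone classed as smoking at interview.

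**Step 6. Number of events.** At the design rates, 134 × 0.01 = 1.3 control and 134 × 0.08 = 10.7 intervention successes. The trial would be decided on about a dozen events, so entry and classification need care. This gives no estimate of bias.

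**The case against.** **The recruitment issue is disclosed.** It is the first limitation named, with training and supervision attached, and the sentence quoted from Randomization concerns delivery of the brief intervention rather than allocation concealment as such. Both observations are correct. But unbiased delivery is exactly what cannot be assured once the arm is known, the Unblinding section's timing fails with it, and disclosure in one section leaves the other two unqualified.

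**Assessors may never know the arm.** A reader might infer that assessors learn the arm at the 2-month call. The documents do not support that. Assessors are to be blind to study design as well as allocation; everyone is encouraged to use NRT and given the Quitline number; controls may refer themselves; and the article does not say that one assessor follows a participant through. What stands is narrower: the answers can indicate the likely arm, and nothing stated keeps a person who heard them from making the later call.

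**Fragility of the result.** A reader might also infer from the small event counts that a shift of one or two participants would carry the result across 0.05. Fisher's exact test at 134 per arm does not bear this out in general. The rounded expected table, 1 vs 11, gives p = 0.005. One participant moved gives 0.010 (1 vs 10) or 0.019 (2 vs 11). Two moved gives 0.019 (1 vs 9), 0.034 (2 vs 10) or, in the single case of two extra control successes, 0.051 (3 vs 11). Fisher's test is not the planned analysis, and such shifts towards the null are not the direction usually feared from an unblinded assessor.

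**The remedies are partial.** Enrolling current residents first does not reach people who move in later, and short-term programs supply 150 of the 210 residents (71%). A sensitivity analysis resting mainly on the 150 individually randomised participants would have very few events. Both points are accepted. The second is a reason not to rely on such an analysis.

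**Conclusion.** The point holds in two parts of unequal strength.

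The recruitment part is a contradiction within the article. For residents enrolled after their site's arm is known, up to 210 of 360 (58%) or 194 on the first-enrolment assumption, entry and the brief intervention are not blind to allocation, contrary to what Randomization and Unblinding say without qualification.

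The assessor part is conditional. The statement that assessors stay blinded until study completion is not secured at 5 and 8 months, because question order works only within a call. It becomes a problem where the same assessor, or one able to see earlier process answers, makes the later call; the article does not settle whether that happens. CO testing limits the effect without removing it.

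Neither the direction nor the size of any bias can be computed from the document. The sample size is unaffected.

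**What to change.** **Recruitment at residences.**
- Complete consent, baseline and brief intervention for all current residents before the site's allocation is released to the peer worker.
- Adjust the primary analysis for baseline HSI, which Table 1 already collects.
- Report numbers approached and consented by arm at cluster sites.
- Qualify the Randomization and Unblinding sections: for residents who enter after release, the peer worker may know the arm.

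**Outcome assessment.** Either have the trial coordinator, who is already unblinded, collect the Quitline, NRT and WAIT-3 items separately, or assign the 8-month call to an existing assessor who has not interviewed that participant and cannot see earlier process forms. Restate the blinding claim to match the option chosen.

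**Cost.** Modest rostering work, form permissions, one covariate and some rewording. Some participants may prefer a familiar assessor. New entrants to short-term sites remain exposed, and the revised text should say so.

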### Blinding

Outcome assessors will be blinded to study design and allocation and will have training and regular supervision on practices to maintain blinding in a PROBE design study. These have been previously used successfully by our team (63). Importantly, outcomes assessors will ask participants about smoking outcomes prior to any questions about use of cessation supports, questions that often produce answers which can indicate likely experimental condition.

The mental health practitioners, follow-up assessors, qualitative interviewers, and Quitline counselors are located in separate organizations, which will maximize maintenance of the outcomes assessors' blindness to study design and treatment allocation. Outcomes assessors will access only contact details, and not treatment files. The eCRF permissions will not allow outcomes assessors to access information about the participant's treatment allocation.

Participants will be aware of what support they are receiving, but not of the comparison condition due to the “limited disclosure” approach. Participants will be informed about what is involved (i.e., the follow-up assessments) and that they may be offered support with smoking cessation. They will not be informed of the specifics of the support (i.e., intervention will receive proactive referral to Quitline and be supplied with NRT). Control participants will be informed of the options available and encouraged to follow up on any they are interested in, in the usual manner (GP/other health professional/self-referral to Quitline). The outcomes assessment team will remain blinded to treatment allocation until completion of the study. Data analysts will be blinded by labeling the intervention conditions “A” and “B.”

### Unblinding

Following baseline assessment and delivery of the brief intervention, peer workers, the trial coordinator, quitline counselors, qualitative staff, and associated investigators will be unblinded to treatment allocation**.**

### Stepwise Procedures

This protocol is presented in accordance with the 2013 SPIRIT (Standard Protocol Items: Recommendations for Interventional Trials) Statement (see Supplementary Material). The schedule of enrolment, interventions, and assessments is summarized in Table 2.

**Table 2 T2:** Stepwise procedures.

**Contact/visit**			**Intervention period**								**Follow-up period**							
**Week**	**−1**	**0**	**1**	**2**	**3**	**4**	**5**	**6**	**7**	**8**	**9**	**10**	**…**	**21**	**22**	**…**	**34**	**35**
Visit number		1									2			3			4	
**ENROLLMENT**																		
Screening (inclusion/exclusion)	X	X																
Informed consent	X	X																
BASELINE ASSESSMENT		X																
Standard smoking care		X																
Randomization		X																
**INTERVENTION^*^**																		
Referral to Quitline		X																
Contacted by Quitline and smoking cessation initiated			X															
Quitline determines preferred oral NRT for second 4-week supply				X														
NRT dispensing		X		X														
Smoking cessation program			X	X	X	X	X	X	X	X								
FOLLOW-UP ASSESSMENTS											X			X			X	
Blinded follow up assessment conducted (all participants)											X			X			X	
Potential qualitative interviewees identified^**^											X			X			X	
Qualitative interviews conducted^**^												X			X			X
CO monitoring (on reported abstainers)																	X	
**ADVERSE EVENTS**																		
Unprompted (serious/severe)			X	X	X	X	X	X	X	X								
Prompted (all)											X			X			X	

* *Intervention group only*.

** *Participants will be purposely selected at each of the assessment timepoints (2, 5, and 8 months) to be invited for interview*.

### Data Management

All data will be entered electronically via eCRF using (REDCap) tools (64) hosted at Hunter New England Local Health District on a secure server. Redcap is a secure, web-based application designed to support data capture for research studies providing an intuitive interface for data entry, audit trails for tracking data manipulation and export, automated export procedures for downloads to statistical packages and procedures for importing data from external sources. The lead investigator (and/or delegate) and study coordinators will conduct ongoing data checking and cleaning.

Participants' personal details will be accessed, used, and stored according to relevant legislations. Access to external health data (e.g., Quitline, MBS/PBS, health records) will only occur with the consent of the participant in accordance with protocols of relevant external agencies (e.g., Commonwealth Department of Human Services for MBS/PBS data). The trial conduct and safety data will be monitored by a Data Safety Monitoring Board (DSMB).

### Statistical Methods

#### Primary and Secondary Outcomes

Independent and blinded statisticians from the CReDITSS Unit at the Hunter Medical Research Institute, Australia, supervised by [name], will conduct analyses of the primary and secondary outcomes.

Analyses will be carried out using a cluster randomized trial framework where the individuals (*n* = 150) are treated as clusters that contribute only one person, the short-term residential programs are clusters that contribute an average of 15 people each (10 programs × 15 people/program = 150 total) and the long-term programs are clusters that contribute 10 people each (6 programs × 10 people/program = 60). We will use a generalized linear mixed model (linear regression for continuous outcomes and logistic regression for dichotomous outcomes) to handle the clustering and the repeated measures at baseline, 2-, 5-, and 8-months; individuals will be modeled as random effects, cluster as a random effect, and group assignment as a fixed effect. Mixed models allow for missing data for the primary intention to treat analysis, but a sensitivity analysis using a worst case scenario (baseline value for continuous outcomes or relapse for dichotomous outcomes in case of missing value) will also be carried out.

Intervention participants who do not complete the intervention, and participants who miss an assessment follow-up time point, will be kept in the study and contacted for later assessments (unless they choose to withdraw from the follow-up assessments).

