### Eligibility Criteria

Participant inclusion criteria are: aged at least 18 years; residing in Victoria; smoking at least 10 cigarettes per day; and accessing treatment or support from participating mental health agencies. Exclusion criteria are: current engagement in Victorian Quitline's callback service; no ready access to a telephone; inability to complete informed consent and/or the screening survey; acute suicidality; myocardial infarction or unstable arrhythmia or angina within the previous 2 weeks (NRT contraindications); and pregnancy (as smokers who are pregnant already receive a different extended Quitline callback service).

Around three-quarters of individuals accessing mental health services own mobile phones (34). Landlines will be used where people do not own mobile phones, as in our previous studies (25, 35).

Quitline counselors: Experienced quitline counselors who have been provided with specialist training on counseling people with mental health issues, and who have demonstrated competence in this work have been allocated to the study (one dedicated counselor per caller for all calls, or to co-ordinate with a substitute where they may be unavailable for some calls).

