**SMOKING MEASURES:**				
Current smoking and quit attempts	X	X	X	X
7 day point prevalence abstinence (self-reported)		X	X	X
6 month prolonged abstinence (primary outcome)				X
CO Monitoring (those reporting abstinence)				A
Heaviness of Smoking Index	X	S	S	S
Tobacco types	X			
Cost	X	S	S	S
History (age first smoked)	X			
Social influences	X			
Cravings	X	X	X	X
Smoking use motives	X			
Situations not allowed to smoke		X	X	X
Goal	X			
Motivation to quit	X	S	S	S
Confidence to quit	X			
Self-efficacy		X	X	X
Products/services to help quit (including NRT, Quitline)	X	X	X	X
Nicotine replacement products (helpfulness, likely use)	X			
Counseling preference (in person or telephone)	X			
Minnesota Nicotine Withdrawal Scale (only two items in follow ups)	X	X	X	X

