#### Primary Outcome

The primary outcome is defined as continued abstinence from smoking since the end of the treatment period, i.e., 6 months sustained abstinence, with no relapse (defined as 7+ days of continuous smoking, and no reported smoking in the last week), with biochemical verification at 8-month follow-up. Sustained abstinence will be assessed via the following question: “When did you last smoke a cigarette, even a puff?” If a participant reports prolonged abstinence at the 8 month follow up, and no smoking in the last week, they will be asked to attend a face to face visit to complete CO testing for objective validation using a Micro+ Smokelyzer, with a reading of 8 ppm or higher defined as indicative of recent smoking.

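### A repeated-measures mixed model is prescribed for a primary outcome that exists only at 8 months, so the primary test is not defined and missing outcomes are simply dropped

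*Protocol article*

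**What the plan says.** The Statistical Methods section of the protocol article, under Primary and Secondary Outcomes, says that blinded statisticians "will conduct analyses of the primary and secondary outcomes" and then gives one model family for all of them: linear for continuous outcomes, logistic for dichotomous ones. The model is meant "to handle the clustering and the repeated measures at baseline, 2-, 5-, and 8-months; individuals will be modeled as random effects", with cluster also random and group fixed. No separate model is given for the primary outcome.

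On missing data the same section states: "Mixed models allow for missing data for the primary intention to treat analysis". The sentence goes on to add a worst-case sensitivity analysis, using "baseline value for continuous outcomes or relapse for dichotomous outcomes in case of missing value". The Exploratory Analyses section adds that different imputation strategies will be explored.

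The Primary Outcome section defines the endpoint as "continued abstinence from smoking since the end of the treatment period, i.e., 6 months sustained abstinence", "with biochemical verification at 8-month follow-up". In Table 1, the row "6 month prolonged abstinence (primary outcome" is marked in the 8-month column only. Eligibility Criteria requires "smoking at least 10 cigarettes per day" at entry.

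**The concern.** A repeated-measures model needs the same outcome at several visits. This outcome cannot exist at baseline, when everyone smokes. It cannot exist at 2 months, when the abstinence window is only opening, or at 5 months, when the window is about half complete. The binary measure that is repeated over follow-up is 7-day point prevalence abstinence, which is secondary.

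Two things follow. The stated model contains a variance component that this outcome cannot inform. And the reason given for not handling missing data further does not apply to it: a mixed model uses a participant's other rows of the same outcome, and here there are none. At stake is the trial's main comparison, in which few events are expected and the choice of model and missing-data rule can matter.

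**Working it through.** **Inputs.** From Sample Size Determination: 1% against 8% abstinence, p = 0.05 (taken as two-sided), 80% power, 134 per arm, about 30% attrition, 191 per arm, 382 in total. From Statistical Methods: 150 individuals treated as one-person clusters. From Table 1 and Primary Outcome: one binary value per person, at 8 months.

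**1. The plan's own figure.** Two proportions, unpooled variance: n = (1.960 + 0.842)² × (0.01 × 0.99 + 0.08 × 0.92) / 0.07² = 133.75, so 134 per arm. Then 134 / 0.70 = 191.4, stated as 191. The plan's figure is reproduced. It is a single-time-point comparison among completers, not a repeated-measures calculation.

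**2. Can the individual variance be estimated?** Expected events among completers are 134 × 0.01 = 1.3 and 134 × 0.08 = 10.7. Take 1/134 against 11/134 as an illustration, one row per person, and fit a logistic model with a normal individual intercept whose standard deviation (SD) is fixed in turn. Cluster effects are left out for simplicity; including them adds no within-person replication.

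| Individual SD | Maximum log-likelihood | Conditional odds ratio |
|---|---|---|
| 0 | -43.929 | 11.9 |
| 0.5 | -43.929 | 12.1 |
| 1 | -43.929 | 13.2 |
| 2 | -43.929 | 20.4 |
| 3 | -43.929 | 42.6 |

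The fit is identical for every SD, while the odds ratio more than triples. The data cannot choose among these values. For the 150 singletons the individual and cluster effects are also the same term.

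**3. Who is analysed.** A participant without 8-month status has no other row of this outcome and contributes nothing. Lost: 0.30 × 382 = 115. Analysed: about 2 × 134 = 268, or 70%.

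**4. Effect of equal attrition, if everyone lost is smoking.**
- Rates among all randomised: 0.08 × 0.70 = 5.6% and 0.01 × 0.70 = 0.7%. The completer rates are higher by 1 / 0.70 = 1.43.
- Risk ratio: 8 / 1 = 8 among completers and 5.6 / 0.7 = 8 among all randomised.
- Odds ratio: (0.08/0.92) / (0.01/0.99) = 8.6, against (0.056/0.944) / (0.007/0.993) = 8.4.
- Power (normal approximation, pooled variance under the null, clustering ignored): 79% with 134 per arm at 1% against 8%; 78.5% with 191 per arm at 0.7% against 5.6%.

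**5. Effect of unequal attrition.** The protocol gives no retention by arm, so this is an assumption. If everyone lost is smoking, the completer risk ratio equals the risk ratio in all randomised times (control retention / intervention retention). With 80% retained in control and 60% in intervention, the factor is 0.80 / 0.60 = 1.33. With the arms reversed it is 0.60 / 0.80 = 0.75.

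**The case against.** The strongest reply is that the paragraph is a condensed description covering several kinds of outcome, and that its natural reduction for a single binary value is a logistic model with group fixed and cluster random, which an analysis plan would spell out. Much of this stands. A reader might infer that no primary model can be fitted at all, and the documents do not support that. In a simulation of the reduced model using the planned cluster sizes (assumed cluster SD 0.5, 30% missing), a finite estimate was obtained in about 75% of runs. The failures came mainly from the roughly 25% of runs with no control-arm events, which is a sparse-data matter. But the reduced model is not the one stated: the text explicitly names four visits and an individual effect, and explicitly ties the missing-data claim to the primary analysis. That is a stated rule that does not fit, not detail left for later.

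Other stronger readings also go too far:
- That missing data are ignored. The missing-as-relapse analysis keeps everyone randomised, and imputation work is promised. These are, however, sensitivity and exploratory analyses.
- That the missing-data statement is worthless. It is reasonable for outcomes measured repeatedly. For the primary outcome, the completer analysis is still valid if missingness depends only on arm and cluster, but that is all the mixed model offers.
- That people with a documented relapse who are then lost will be discarded. No section says so, and the outcome definition would allow them to be classed as failures. The article does not say that either.
- That the treatment effect is inflated by 1.43. That factor applies to absolute rates; under equal attrition the risk ratio is unchanged.

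**Conclusion.** The point holds in this form. The stated model does not define the primary test, because its individual random effect is not identifiable from one binary value per person. For this outcome the mixed model gives no protection against missing data beyond a complete-case analysis of about 268 of 382 participants, despite the intention-to-treat label.

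The practical size is moderate. With equal 30% attrition and all those lost smoking, relative effect and power are nearly the same either way. What is exposed is the absolute abstinence rate in each arm and, if dropout differs by arm, the comparison itself. The protocol gives no basis for predicting the size or direction of that difference. Missing-as-smoking can also be biased when dropout differs by arm, so choosing between it and multiple imputation is a genuine trade-off. What matters is that one is named in advance.

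**What to change.** For the primary outcome, specify a single-time-point analysis at 8 months: one row per participant, group as fixed effect, cluster as a random effect (or cluster-robust standard errors), no individual random effect, and no baseline, 2- or 5-month rows.

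Before applying any missing-data method, code as failure anyone whose 5-month or other post-treatment data already show relapse as the Primary Outcome section defines it. For the remaining missing outcomes, name one primary rule that retains all randomised participants, either missing counted as smoking or multiple imputation using 2- and 5-month smoking status, with the other as sensitivity analysis.

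Limit the repeated-measures mixed model, and the statement that it allows for missing data, to outcomes measured repeatedly.

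The cost is analysis wording only, with no new data collection. Reported abstinence rates will be slightly lower than among completers.
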